## Abstract

Exercise may be an effective tool to improve symptoms and quality of life in those with endometriosis. However, the optimal dose to elicit such changes is unknown. This study will explore the critical threshold of exercise dose required to elicit symptomatic and biomarker changes in women with endometriosis, particularly for those who may be disadvantaged through spatial and aspatial factors.

Fifty women with clinically confirmed endometriosis will be randomly allocated into one of four groups: a passive control, active control (yoga), short duration walking and yoga, long duration walking and yoga.

Participants in the three active groups will complete 12 weeks of exercise.

Symptom severity (chronic) and biomarkers will be assessed pre-post intervention; adherence, and symptom impact (acute) will be assessed each week.

## Specifications table

**Table utbl0001:** 

**Subject area**	Medicine and Dentistry
**More specific subject area**	Exercise Physiology
**Name of your protocol**	Exploring the exercise dose to induce symptomatic and biomarker change in endometriosis: A protocol for a randomised controlled trial.
**Reagents/tools**	Not applicable
**Experimental design**	This study will adopt a prospective, parallel randomized controlled trial design. Fifty women with clinically confirmed endometriosis will be randomly allocated into one of four groups: a passive control, active control (yoga), short duration walking and yoga, long duration walking and yoga. Participants in the three active groups will complete 12 weeks of exercise; symptom severity (chronic) and biomarkers will be assessed pre-post intervention; adherence, and symptom impact (acute) will be assessed each week. A combination of piecewise (segmented) mixed-effect regression, mixed model analysis and *t*-tests will be applied for analysis.
**Trial registration**	This protocol has been approved for registration on the Australian and New Zealand Clinical Trials Registry (ACTRN12625001442493p)
**Ethics**	Participants will be required to provide written and verbal consent following an outline of all procedures. This study conforms to the Declaration of Helsinki and Charles Sturt University’s Human Research Ethics (H25454) and Biosafety
**Value of the Protocol**	The protocol specifically itemizes the exercise prescription for women with endometriosis, allowing validation and enquiry in the field. The protocol is a self-directed home-based exercise intervention, which may promote adherence and longevity. The exercise prescription is low intensity with a low equipment requirement and can therefore assist in the servicing of disadvantaged populations. Both quantitative and qualitative data are collected, which will allow for a comprehensive, mixed methods assessment of the intervention both in terms of its effectiveness and feasibility / acceptability.

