### Survey data

Demographic information, current exercise behaviours (APSS), scores of depression, anxiety and stress (DASS-21), health-related quality of life (EHP-30), sleep (PSQI), self-efficacy (SEE) and open-ended questions regarding treatment, geographical location, fertility and access to care, will be collected pre- and post-intervention. Moreover, symptoms will be tracked weekly via the Endometriosis Impact Scale (EIS) through REDCap, a survey administration software program.

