## Data analysis

All data will be de-identified for analysis and reporting. The estimated sample size was determined using data from Gonçalves et al.[25] where the mean difference for pain between the control and intervention was 24.74, for an effect size of d = 1.33 and comparisons between four groups, a sample size of 32 was estimated (alpha at 0.05 and power 0.80). Factoring in attrition and funding availability, the target sample size was set to 50. However, a piecewise (segmented) mixed-effect regression will be used to determine the critical threshold for exercise dose (primary outcome). Exercise dose (all randomized participants) will be determined by duration and intensity (heart rate) variables, aggregated weekly. For a sample of 50 participants across 12 weeks, with a mixed-effects piecewise model, there will be a minimum of 600 observations, which provide sufficient power and stability for this type of analysis[26]. Threshold and detectable change in slope will be determined by Y^t^ = B^0^ + B^1^* time^t^ + b^2^ * intervention^t^ + b^3^ time after intervention^t^ + e^t^, and confirmed with Davies Test. Intercurrent events such as medication changes, clinical exacerbations and poor adherence will be time- and date-stamped for consideration as co-variates in the regression analysis.

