All other data will be reported as mean ± standard deviation (SD) or median interquartile ranges. Normal distribution will be determined by Shapiro-Wilk’s test and non-normally distributed data will be logarithmically transformed prior to analysis. Pain, as a subset of the EHP-30 is the primary endpoint and will be analysed with an intention-to-treat analysis. A sensitivity (per-protocol analysis) will also be conducted to confirm outcomes. Secondary and exploratory endpoints will be arranged hierarchically as follows; quality of life (EHP-30), depression, stress, anxiety (DASS-21), functional capacity, sleep (PSQI), estradiol, CRP, cortisol. Multiple comparisons will be adjusted for using the Benjamini-Hochberg false discovery rate procedure. Missing data will be managed depending upon the volume of data, complete case analysis will be performed (<5%) for 5–40%, multiple imputation for chained equations or random forest imputation will be employed. Complier average causal effect (CACE) analysis will be employed if compliance varies significantly. Significance will be set at p < 0.05. All statistical procedures will be performed using Statistical Package for the Social Sciences (SPSS; Windows version 31.0, Chicago, IL, USA) and R Studio (2026.07.1).

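### The tools named for the pre-post pain endpoint do not commit to baseline adjustment, although baseline EHP-30 pain is collected and arms of about 12 women need the precision

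*Protocol article*

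**What the plan says.** The specifications table (Experimental design) lists the methods, the first of them in piecewise (segmented) form: "mixed-effect regression, mixed model analysis and *t*-tests will be applied for analysis". It does not say which method serves which outcome.

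Data analysis fixes the endpoint: "Pain, as a subset of the EHP-30 is the primary endpoint and will be analysed with an intention-to-treat analysis". It names no model, contrast or covariate for that analysis. Under Survey data, the EHP-30 belongs to the set of instruments that "will be collected pre- and post-intervention"; the weekly symptom instrument is a different one, the EIS.

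Data analysis does discuss covariates, but only these: "Intercurrent events such as medication changes, clinical exacerbations and poor adherence will be time- and date-stamped for consideration as co-variates in the regression analysis". All three examples arise after randomisation.

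The same section also describes a dose analysis: "a piecewise (segmented) mixed-effect regression will be used to determine the critical threshold for exercise dose (primary outcome"), with the dose variable defined as follows: "Exercise dose (all randomized participants) will be determined by duration and intensity (heart rate) variables, aggregated weekly".

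Exercise intervention specifies simple randomisation to four groups. It mentions no stratification and gives no allocation ratio.

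**The concern.** EHP-30 pain gives two values per woman. The piecewise model is justified by at least 600 observations (50 women × 12 weeks), so as described it is not an analysis of EHP-30 pain. Of the listed tools, that leaves the mixed model and the t-tests. Neither, as named, commits the trial to conditioning on baseline pain, and some common forms of both do not.

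Precision is at stake, and so is the chance of misreading a baseline imbalance as an effect. Fifty women in four arms is about 12 per arm, and the design does not balance pain between them. If two arms happen to differ in pain at the start, a post-score comparison carries part of that gap into the result. A change-score comparison over-corrects for it whenever r is below 1. Leaving the form open also leaves a later choice between post-score, change-score and mixed-model results for the primary endpoint.

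**Working it through.** **Inputs from the protocol (Data analysis):** mean difference in pain 24.74, d = 1.33, alpha 0.05, power 0.80, N = 32 before attrition, target N = 50. Implied SD = 24.74 / 1.33 = 18.6 points.

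**Assumptions:** r is not given, so 0.3, 0.5 and 0.7 are used. Arms are equal (50 / 4 = 12.5, taken as 12), there is no attrition, tests are two-sided at 0.05, and d is in units of the post-score SD.

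**The plan's own figure.** N = 32 reproduces in two ways. A four-group one-way ANOVA with f = d/2 = 0.665 has power 0.85 at N = 32. A one-sided two-sample t-test at d = 1.33 with 8 per arm has power 0.81, and 8 × 4 = 32. Neither uses a baseline covariate.

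**Relative variance of the between-arm difference**

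| r | post score: 1 | change: 2(1 − r) | baseline-adjusted: 1 − r² | saving over change |
|---|---|---|---|---|
| 0.3 | 1.00 | 1.40 | 0.91 | 35% |
| 0.5 | 1.00 | 1.00 | 0.75 | 25% |
| 0.7 | 1.00 | 0.60 | 0.51 | 15% |

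A group-by-time mixed model on two time points with free baseline means tests the difference in change, so it belongs in the change column when data are complete.

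**Pairwise power.** Noncentrality = d × √(n/2) / √v, where v is the relative variance. Degrees of freedom are 2n − 2 unadjusted and 2n − 3 adjusted. With n = 12, d = 1.33 gives 1.33 × √6 = 3.26 unadjusted and 3.26 / √0.75 = 3.76 at r = 0.5. For d = 0.8 the values are 1.96 and 2.26.

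| n per arm | d | post-score t-test | adjusted, r = 0.3 / 0.5 / 0.7 | change-score t-test, r = 0.3 / 0.5 / 0.7 |
|---|---|---|---|---|
| 12 | 1.33 | 0.88 | 0.90 / 0.95 / 0.99 | 0.75 / 0.88 / 0.98 |
| 12 | 0.8 | 0.47 | 0.50 / 0.58 / 0.74 | 0.35 / 0.47 / 0.68 |
| 8 | 1.33 | 0.70 | 0.73 / 0.81 / 0.93 | 0.55 / 0.70 / 0.89 |

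These are two-arm comparisons. Pooling the error over all four arms raises the adjusted values slightly (for example 0.58 becomes 0.60 at n = 12, d = 0.8, r = 0.5).

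**Chance imbalance.** The SD of a baseline difference between two arms of 12 is √(2/12) = 0.41 SD units. The probability that a given pair differs by more than 0.5 SD is therefore about 22%. With 8 per arm it is about 32%.

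**The case against.** **Silence is not an error.** This is a condensed article, and a covariate list is commonly left to an analysis plan that is not shown. Nothing in the text forbids baseline adjustment. A mixed model on pre and post data can recover the efficiency if baseline means are constrained to be equal. This stands in part: the protocol does not fix an unadjusted analysis. But it does name its tools, including t-tests, and it does discuss covariates, naming only post-randomisation ones. Stating the form would settle the matter.

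**The t-tests may be meant for something else.** A reader might infer that the arms will be compared on pain by t-tests, perhaps in six pairwise tests. The documents do not support that. The specifications table assigns t-tests to no endpoint, and no number of pairwise comparisons is stated.

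**The plan does use dose.** A reader might infer from the unordered list of methods that the dose question is ignored. It is not: a dose-threshold regression is a headline analysis. What is true is narrower. That regression is described in terms of recorded weekly dose, so it is not the randomised comparison of arms on EHP-30 pain.

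**A linear trend across arms should be the primary test.** This is tempting, but the trial looks for a threshold and the gain depends on an unknown shape. At 8 per arm, unadjusted, with evenly spaced means up to 1.33 SD, trend power is 0.77 against 0.58 for the omnibus F-test. If both walking arms gain 1.33 SD and the other two do not, trend again leads, 0.90 against 0.85. If only the top arm responds, or yoga alone gives the full effect, trend has 0.68 against 0.72. Both of these last shapes are monotone.

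**The gain is modest where planned.** At 12 per arm and d = 1.33, a raw t-test already has power 0.88. That also stands; the adjustment matters most if the true effect is smaller than that large planning value or if attrition is heavy.

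**Conclusion.** The concern holds in a limited form. For the randomised comparison on the primary pain endpoint, the named tools do not commit to using baseline pain, which is already collected. Adjustment cuts variance by 9% to 49% relative to a post-score comparison, and by 35% to 15% relative to a change-score comparison, as r goes from 0.3 to 0.7. With 12 per arm and r = 0.5, power rises from 0.88 to 0.95 at d = 1.33 and from 0.47 to 0.58 at d = 0.8; across the range of r, the second figure runs from 0.50 to 0.74.

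These sizes rest on the assumed r, equal arms and no attrition. Simple randomisation can leave arms unequal, and losses would lower every power quoted. The documents do not show whether d = 1.33 was standardised by a post-score or a change-score SD. This is an inexpensive improvement in precision and pre-specification, and not a sign that the planned analysis would be invalid.

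**What to change.** State in Data analysis that the intention-to-treat comparison of post-intervention EHP-30 pain is a linear model on randomised arm with baseline EHP-30 pain as covariate, or a mixed model with a common baseline mean across arms. Report adjusted between-arm differences with 95% intervals. Say that t-tests are not used for this between-arm comparison, and align the specifications table. A trend contrast across the four arms may be added as a supportive analysis, but should not be required as the primary test.

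The cost is a change of wording and one degree of freedom. No new data are needed, because baseline EHP-30 is already in the schedule.

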## Background

Recognized globally as a debilitating condition, endometriosis is a systemic disease involving endocrine, immune-inflammatory and proangiogenic processes[1]. While dysregulation in hormone-receptor signaling and immune-inflammatory pathways[2] are protagonists underlying symptom severity; neurogenesis, central sensitization, fibrosis, the location and size of endometriotic lesions, the organ systems affected, and the presence of comorbidities highlight the complexity of this condition. While the treatment of endometriosis is dictated by the chief complaint or primary indication[3], the most common forms of treatment are pharmacological and surgical. However, the reduction in symptoms is transient in nature; when medications are ceased, symptoms frequently return and further, post-operative recurrence is common[4]. Moreover, the economic burden associated with endometriosis can amount to $20 898 international dollars, per person, per year[5]. This impact is attributed not only to diagnosis and management, but also productivity losses[5,6]. When combined with spatial and aspatial factors that impact access to appropriate and timely treatment, such as geographical location, income and ethnicity[7], management of endometriosis becomes quite complex. Accordingly, further inquiry into potential alternative and sustainable management strategies is warranted.

Recent evidence suggests the management of endometriosis requires a multidisciplinary, life-course approach[8], extending beyond the reproductive system and incorporating physical and psychosocial elements, whilst acknowledging patient autonomy and self-management strategies[8].The importance of exercise and physical activity has gained increasing awareness as a viable non-pharmacological, non-surgical adjunct management strategy to support the quality of life of individuals with endometriosis[9]. Specifically, a recent meta-analysis reported physical activity and exercise to have beneficial effects on pain, quality of life, control and powerlessness and emotional well-being[10]. Exercise is widely recognized as an effective therapeutic intervention for pain management, fertility, cardiometabolic health, menstrual symptoms, indices of quality of life and improvement in inflammatory profiles[[11], [12], [13], [14], [15], [16]]. The potential of exercise to improve symptoms and quality of life in women living with endometriosis may be associated with immune and inflammatory modulation, regulation of autonomic function, musculoskeletal adaptations and reductions in central sensitisation[9]. However, globally, there are limited studies exploring specific exercise prescription (modality, volume, frequency and intensity) to improve symptoms, inflammation and quality of life. While emerging evidence suggests exercise has the capability to exert positive effects on symptoms, quality of life, biomarkers and even lesion size in endometriosis[[15], [16], [17], [18], [19], [20], [21], [22], [23]], to validate these findings, greater exploration into the exercise dose is required.

This study protocol has been designed to elucidate the critical threshold of exercise dose required to elicit changes in symptoms, quality of life, and biomarkers of endometriosis. By specifically detailing the exercise prescription, this protocol builds the evidence base for further scientific enquiry into exercise management in endometriosis. Further, this protocol provides clinical guidance to health and exercise professionals.

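### The critical-dose aim extends to quality of life and biomarkers, but these are measured only twice and the one described threshold analysis needs weekly data

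*Protocol article*

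**What the plan says.** **Aim.** The Background says the protocol is designed to "elucidate the critical threshold of exercise dose required to elicit changes in symptoms, quality of life, and biomarkers of endometriosis". The Abstract puts it as the "critical threshold of exercise dose required to elicit symptomatic and biomarker changes in women with endometriosis", without quality of life.

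**Measurement times.** The Abstract states: "Symptom severity (chronic) and biomarkers will be assessed pre-post intervention". The Specifications table repeats this. Under Survey data, the EHP-30 is also a pre and post measure, and only the Endometriosis Impact Scale (EIS) is recorded each week.

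**Threshold analysis.** Data analysis assigns the critical threshold to a piecewise mixed-effects regression, with dose aggregated by week. Its justification is: "For a sample of 50 participants across 12 weeks, with a mixed-effects piecewise model, there will be a minimum of 600 observations". The printed equation has an intercept, time, intervention and time after intervention.

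**Other outcomes.** Data analysis names EHP-30 pain as the primary endpoint and ranks the rest as secondary and exploratory: "quality of life (EHP-30), depression, stress, anxiety (DASS-21), functional capacity, sleep (PSQI), estradiol, CRP, cortisol". Besides the piecewise model, the Specifications table names mixed models and t-tests.

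**The concern.** The article fixes an aim, a measurement schedule and a method, and the three do not fit together. The aim asks at what dose symptoms, quality of life and biomarkers begin to change. The method meant to answer it draws on twelve weekly records per woman. Two of the three domains have one value before and one after. So do the symptom severity measures that the Abstract calls chronic, including the EHP-30 pain score.

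A separate statistical analysis plan could add a model but could not add measurement times. If the aim stays as worded, one of two things follows. Either the quality-of-life and biomarker part of the question goes unanswered, or someone fits a breakpoint to about 50 change scores afterwards and reports it as a critical dose. The second matters because the Background offers the work as guidance for health and exercise professionals.

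**Working it through.** **1. The plan's own figure.** 50 women x 12 weeks = 600. This reproduces exactly, and it can apply only to an outcome recorded weekly. The article does not name the outcome in the equation. That it is the weekly EIS is an inference from this count.

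**2. The count for outcomes measured twice.** 50 x 2 = 100 records, or at most 50 change scores.

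**3. Can the printed model be fitted?** Read the equation as a time series with a break at week k. The columns are 1, t, an indicator for t > k, and max(t - k, 0).

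- Weekly data, t = 1 to 12, with k = 3, 6 or 9: rank 4 of 4.
- Pre and post data, t = 0 and 12, same k: rank 2 of 4.

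Two time points supply only two distinct rows, so the change in level and the change in slope cannot be separated from the intercept and the overall slope. If the intervention term is instead read as an arm label, the four terms can be estimated from two time points, but the model is then an arm-by-time comparison with no breakpoint. Neither reading gives a threshold for these outcomes.

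**4. Do the other named analyses fill the gap?** Mixed models and t-tests compare means between arms or times. The complier average causal effect analysis is conditional and concerns compliance. None of them locates a breakpoint.

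**5. What would a post hoc breakpoint be worth?** This is an illustration, not a test of anything planned. Mean prescribed minutes per week over 12 weeks, from Exercise intervention:

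- passive control: 0
- yoga: 3 x 10 = 30
- shorter walking plus yoga: (60 + 90)/2 + 30 = 105
- longer walking plus yoga: (120 + 150)/2 + 30 = 165

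Assumed inputs, not in the article: adherence mean 80% (SD 20%); incidental exercise mean 14 min per week; one change score per woman with SD 1; true threshold at 60 or 100 min per week; benefit at 165 min of 0.8 or 1.33 SD (the larger value is the article's d for pain). The fit is segmented least squares over a grid of 15 to 165 min, with the critical value simulated under a straight-line dose response, 1,500 trials per scenario.

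| Result, range over scenarios | n = 50 | n = 32 |
|---|---|---|
| Power of the breakpoint test | 7% to 39% | 7% to 25% |
| Estimate within 30 min of the true threshold | 36% to 54% | 33% to 48% |
| Power of a linear trend across the four arms | 30% to 81% | 18% to 64% |

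At n = 50 the middle 95% of estimates covers the whole 15 to 165 min grid. For scale, a value picked at random from that grid falls within 30 min of either true threshold 60/150 = 40% of the time. Separately written code gave 7% to 41% breakpoint power and 33% to 80% trend power at n = 50. A simulation with other inputs (threshold at 75 min, grid 20 to 160) also returned estimates over its whole grid.

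The two tests ask different things: the trend test looks for any dose gradient, the breakpoint test for a departure from a straight line. The comparison shows which question these data can better answer.

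**The case against.** Several objections have force.

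- **The title.** A reader might infer that the title also promises a critical threshold. It does not. The protocol name is "Exploring the exercise dose to induce symptomatic and biomarker change in endometriosis", which mentions neither a threshold nor quality of life. The point rests on the Background and, for biomarkers, the Abstract.
- **No link to dose at all.** A reader might infer that nothing planned relates these outcomes to dose. That goes too far. The four randomised arms are graded by assigned exercise, and mixed models and t-tests across them compare assigned doses. What is missing is a threshold estimate.
- **The unseen analysis plan.** Models for secondary endpoints are often left to it. So it can be said only that the article describes no ordered trend test, not that none is planned. The two measurement times are fixed either way.
- **The simulation.** No one proposed a breakpoint on change scores. Dose is taken in minutes, whereas Data analysis defines it by duration and heart rate, and the other inputs are assumed. It shows how imprecise the tempting post hoc analysis would be; it does not show that a planned analysis fails.
- **Importance.** Biomarkers come last in the hierarchy, and Limitations already advises caution with them. The planned arm comparison of EHP-30 pain is unaffected. This lowers the severity but does not remove the mismatch.
- **The symptom series.** The printed equation has no dose term, so narrowing the aim to weekly symptoms does not by itself make that part deliverable.

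**Conclusion.** The point holds in a limited form. The stated critical-threshold aim is wider than the data can serve. For quality of life, the three biomarkers and EHP-30 pain, the described threshold model has rank 2 of 4, and no other named analysis estimates a threshold. This follows from the measurement schedule and needs no assumption beyond reading the printed equation as a model in time; under the arm-label reading it contains no breakpoint at all.

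The size of the risk from a post hoc breakpoint (about 7% to 40% power at 50 women, and a location little better than chance) rests on the assumed adherence, incidental exercise, effect sizes and thresholds, and on dose in minutes.

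The randomised comparisons stand. Severity is minor to moderate: it is mainly a correction to the aim, but it changes what the trial may claim.

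**What to change.** 1. In the Abstract and Background, limit the critical-threshold aim to the weekly EIS symptom series, on condition that the piecewise model in Data analysis is written with a dose term.
2. For quality of life and the three biomarkers, restate the aim as a dose-response comparison by randomised arm. Prespecify one ordered trend contrast across the four arms, on post-intervention values adjusted for the pre value. Take the scores from prescribed dose, for example 0, 30, 105 and 165 min per week, with ordinal arm scores as a sensitivity analysis. Minutes count yoga and walking alike and ignore intensity, so they are not the only valid scale.
3. State that no breakpoint will be reported as a critical dose for any outcome measured only twice, EHP-30 pain included.

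**Cost.** Two wording changes and a short addition to the analysis text; no new data. The claim becomes narrower, and the trend test is itself only moderately powered: about 30% to 81% with 50 women under the assumptions above.
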